#### 2.3.2. Procedure and Measures

The researchers aim to conduct a single-blinded randomized controlled trial (RCT) evaluating the effectiveness of grief counseling versus a waitlist control group in reducing prolonged grief symptoms, post-traumatic symptoms, depression levels, and suicidal intentions in bereaved Chinese individuals in relation to COVID-19.

After finishing the baseline questionnaires and signing the informed consent, 160 bereaved participants will be randomly assigned to the grief counseling group or the waitlist group.

The sample size is calculated based on the expected difference on the primary outcome variable (grief symptoms of the bereaved) between the different groups. According to previous RCTs on bereaved individuals [43], we expect a medium Cohen effect size of 0.5 in the intervention group. The sample size calculation is based on the conventional significance (α) and power (1−β) levels of 0.05 and 0.80, respectively, and an expected dropout percentage of 20%. The result shows that we will need almost 80 participants for each group, therefore, we have determined the total sample size to be 160 in this study.

The measures in study three are the same as study three. Assessments will be conducted at three time points: before randomization (baseline, T0), at post-counseling (T1), and three months after the post-counseling (T2).

Table 2 shows which measures will be assessed at each time point. And Figure 1 shows the research process.

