## 3. Statistics Analyses

IBM SPSS Version 25 (Armonk, New York, USA) will be used to analyze the data. Both completer analyses and intention-to-treat analyses (using the method of last observation carried forward) will be carried out. Descriptive characteristics of the sample will be calculated as obtained counts (*n*) and simple proportions (%), with missing items reported as missing.

For study one, the measurements at three different time points will be compared using the analyses of variance (ANOVA) for continuous variables and the chi-square test for categorical variables.

In addition, in study two, the researchers will employ linear regression analyses to examine the predictors of PG-13, DASS-21, PCL-5 and PTGI at each time point, while controlling for gender, age, education level, marital status, and religious beliefs. The cross-lagged model will be used to further clarify the direction of the relationship between the predictors and outcome variables. A *p*-value < 0.05 (2-tailed) will be taken to indicate statistical significance.

For study three, Chi-square tests and ANOVAs will be conducted on baseline scores to rule out significant differences between groups on demographic or loss-related or outcome variables before treatment. The treatment effects on the primary outcome variables will be examined with a 2 (groups) × 3 (time points) multivariate analysis of variance (MANOVA), with three time points (baseline, post-counseling, and three months follow-up) as the repeated measures. The outcomes of treatments will be further investigated separately with the analyses of covariance (ANCOVA), using baseline scores of the outcome variables as covariates.

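### The RCT's lead treatment test counts the pre-randomisation score as one of three responses, so the stated 80% power, which belongs to a simple two-group comparison, is not tied to it

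*Protocol article*

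**What the plan says.** Section 2.3.2 of the protocol article sizes the trial on the "expected difference on the primary outcome variable (grief symptoms of the bereaved) between the different groups". It states "we expect a medium Cohen effect size of 0.5 in the intervention group", the "conventional significance (α) and power (1−β) levels of 0.05 and 0.80", and 20% dropout, and concludes: "The result shows that we will need almost 80 participants for each group". The total is 160. The same section and Table 2 place the baseline assessment before randomisation.

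Section 3 then names the analysis for study three. Treatment effects on the primary outcomes are tested in a design of two groups by three visits, using a "multivariate analysis of variance (MANOVA), with three time points (baseline, post-counseling, and three months follow-up) as the repeated measures". The next sentence says that outcomes are "further investigated separately with the analyses of covariance (ANCOVA), using baseline scores of the outcome variables as covariates". Section 3 plans both completer analyses and intention-to-treat analyses with last observation carried forward (LOCF).

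The article does not say which MANOVA term carries the treatment effect, and it gives no correlation between visits.

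**The concern.** Counseling cannot affect a score taken before randomisation, so the expected group difference at baseline is zero. Using that score as a response affects the two usual terms of a 2 × 3 design differently. The group main effect averages the zero into the treatment difference. The group × time term works on changes from baseline and spends two degrees of freedom. Neither is the comparison for which the sample size was computed. The test that makes efficient use of baseline, ANCOVA, is in the plan but comes second.

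At stake is whether the lead analysis could be negative when counseling has the effect the trial was sized for. If the MANOVA were null and the ANCOVA positive, the order of the text would give the MANOVA the lead.

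**Working it through.** **Inputs from section 2.3.2.** Effect size d = 0.5 between groups, α = 0.05, power 0.80, dropout 20%, 80 per arm. Two-sided testing is assumed for study three: section 3 states it in its study two paragraph ("A *p*-value < 0.05 (2-tailed) will be taken to indicate statistical significance"), and it is needed to reproduce the stated size.

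**Reproducing the plan's figure.** For a two-sided, two-group comparison of means at one time, the normal approximation gives 63 per arm and 63/0.8 = 78.75, so 79. The exact t calculation gives 64 per arm and 64/0.8 = 80. A one-sided test gives 50 per arm before dropout and does not fit. The stated size is therefore that of a simple two-group comparison, with nothing in it for repeated measures or a 2-df test.

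**Assumptions for the rest, not in the article.** One scale at a time; 64 completers per arm; unit SD; group differences of 0, 0.5 and 0.5 at baseline, post-counseling and follow-up; the same correlation r between all visits. Power comes from the noncentral F distribution, with multiplier 64/2 = 32.

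- Group × time (multivariate): noncentrality 32 × 0.1667/(1 − r) = 5.33/(1 − r), on F(2,125).
- Group main effect: mean difference (0 + 0.5 + 0.5)/3 = 0.333 and variance (1 + 2r)/3, so noncentrality 32 × 0.333²/((1 + 2r)/3) = 10.67/(1 + 2r), on F(1,126).
- ANCOVA at post-counseling: noncentrality 32 × 0.25/(1 − r²) = 8/(1 − r²), on F(1,125).
- ANCOVA on the mean of the two follow-up scores: noncentrality 8/((1 + r)/2 − r²), on F(1,125).

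| r | Group × time | Group main effect | ANCOVA, post-counseling | ANCOVA, mean of both |
|---|---|---|---|---|
| 0 | 52% | 90% | 80% | 98% |
| 0.2 | 62% | 78% | 82% | 96% |
| 0.3 | 68% | 73% | 84% | 96% |
| 0.4 | 76% | 68% | 87% | 97% |
| 0.5 | 83% | 63% | 90% | 98% |
| 0.6 | 91% | 59% | 94% | 99% |
| 0.7 | 97% | 55% | 98% | above 99% |

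Group × time reaches 80% at r of about 0.46 and above. The main effect reaches it only at r of about 0.17 and below. In between, neither does.

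**Sensitivity of the group × time threshold.** It rises to about 0.55 if the effect fades to 0.4 at follow-up, and to about 0.59 if it fades to 0.25. With first-order autoregressive correlation and a sustained effect it is about 0.58 for adjacent visits.

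**LOCF set.** This was simulated with 80 per arm, 16 in each arm carrying baseline forward to both later visits.

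| r | Group × time | ANCOVA, post-counseling |
|---|---|---|
| 0 | 51% | 73% |
| 0.2 | 62% | 77% |
| 0.4 | 75% | 82% |
| 0.5 | 82% | 87% |

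**The case against.** A reader might infer that the treatment test misses 80% power unless scores correlate above about 0.45, and that a baseline-adjusted test reaches 80% at any correlation. The article does not support either statement in that form.

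- The threshold belongs to group × time alone, with equal correlations and a sustained effect. For the main effect the dependence on r runs the other way. A literal 3-df test on all three scores keeps at least 89% at every r from 0 to 0.8 under the same sustained effect. The term is not named, so no single threshold can be attributed to the plan.
- No r is given. At r of 0.6 or more with a sustained effect, group × time is within about 3 points of ANCOVA.
- Change from baseline does not always add noise. With equal variances a change score has variance 2(1 − r), which is below that of the raw score once r exceeds 0.5. Part of the loss comes from the 2-df test: a 1-df contrast of mean post-baseline score minus baseline reaches 80% at r of about 0.33.
- ANCOVA at a single visit falls below 80% in the LOCF set at low r. In completers at r of 0 or 0.1, the group main effect has more power than ANCOVA at a single visit.
- Baseline adjustment is already planned, and nothing in section 3 makes the ANCOVA conditional on a significant MANOVA. Group × time is also a valid randomised comparison, so this is a matter of efficiency and not of bias.

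All of this stands. It does not remove the mismatch: the article itself names the lead test, and its power statement was computed for a different one. An unseen analysis plan could name the term, but with 0.5 at both follow-ups neither usual 2 × 3 term reaches 80% across the whole range of r.

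**Conclusion.** The point holds as a mismatch between the sample size and the lead test, and as a matter of the order of two planned analyses. The stated 80% is not tied to the 2 × 3 MANOVA. On the stated assumptions, the possible shortfall for group × time runs from none (r of 0.46 or more) to 28 points (52% against 80% at r = 0). For the main effect it is 17 points at r = 0.5 (63% against 80%).

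Whether any power is actually lost cannot be settled from the article, because r, the MANOVA term and the course of the effect over time are not given. Under a sustained effect in completers, ANCOVA on the mean of the two follow-up scores has at least 96% and is never below either 2 × 3 term over the range computed. This is a low-cost improvement, not proof that the trial is underpowered.

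**What to change.** In section 3, make the ANCOVA already planned the lead treatment test for study three: post-baseline grief score or scores as the response, baseline score of the same scale as covariate. State whether the response is the post-counseling score, the follow-up score or both, for example their mean or a repeated-measures model with baseline as covariate. In section 2.3.2, attach the 80% power statement to that test, and say whether it refers to completers or to the LOCF set. Keep the 2 × 3 analysis as supportive or descriptive and name the term to be reported.

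The cost is wording. Baseline scores and the ANCOVA are already in the plan, and no new data or participants are needed.

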### 2.1. Study 1: Grief Counselor Training and Evaluation

Study one aims to professionally train psychological counselors to be competent to carry out grief counseling. 300 candidates for the program will be recruited. Certain information will be gathered from the candidates, who will be screened for suitability for the program. Training program targeting grief counseling will be designed and implemented to coach these counselors. The training program consists of a basic phase and an advanced phase. A certain competency test will be carried out before the training, and after the two phases of the training to evaluate the effectiveness of the training program.

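### The Study 3 analyses treat counseled participants as independent; if counselors each see several trial clients, the planned tests reject somewhat too often

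*Protocol article*

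**What the plan says.** Section 2.3.2 describes an individually randomized, two-arm trial: "160 bereaved participants will be randomly assigned to the grief counseling group or the waitlist group". Section 3 analyzes the primary outcomes with a 2 (groups) × 3 (time points) repeated-measures MANOVA, followed by covariance analysis: "The outcomes of treatments will be further investigated separately with the analyses of covariance (ANCOVA"), with baseline scores as covariates. No term for the counselor appears in either model.

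The sample size in section 2.3.2 rests on grief symptoms: "The sample size is calculated based on the expected difference on the primary outcome variable". Its inputs are "we expect a medium Cohen effect size of 0.5 in the intervention group", "conventional significance (α) and power (1−β) levels of 0.05 and 0.80, respectively" and "an expected dropout percentage of 20"%. The conclusion is "we will need almost 80 participants for each group, therefore, we have determined the total sample size to be 160".

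On who delivers the counseling, the Abstract says that the project trains counselors for the bereaved, and section 2.1 adds: "Study one aims to professionally train psychological counselors to be competent to carry out grief counseling". Section 2.1 refers to 300 candidates, who are then screened; the Abstract refers to 300 counselors recruited to attend training. Section 2.3 describes 8–10 online sessions of one hour. The article does not give the number of counselors who deliver Study 3, the number of trial clients per counselor, or whether sessions are individual or in groups.

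**The concern.** Counselors differ in effectiveness, and each counseled participant has 8–10 hours of contact. Two participants with the same counselor may therefore have more similar outcomes than two with different counselors. The wait-list arm has no such source of correlation during the comparison. This is a partially nested design: clustering can arise in one arm only.

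A MANOVA or ANCOVA without a counselor term takes every participant as an independent unit. If counselors are shared, the standard error of the arm difference is understated, confidence intervals are too narrow and the null hypothesis is rejected more often than 5% of the time. Baseline adjustment does not cure this, because correlation within counselor can remain in the adjusted residuals. At stake is the validity of the efficacy claim in what section 4 presents as the first evaluation of its kind in mainland China.

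**Working it through.** **Step 1: reproduce the stated sample size.** Inputs from section 2.3.2: d = 0.5, α = 0.05, power 0.80, dropout 20%. Sidedness is not stated for this calculation; two-sided is assumed.

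- Two-sided t-test: 64 per arm, and 64 / 0.8 = 80.
- Normal approximation: 63 per arm, and 63 / 0.8 = 78.75, rounded up to 79.
- One-sided: 50 per arm, and 50 / 0.8 = 62.5, rounded up to 63, which does not match.

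The 80 per group is therefore a two-sided independent-samples figure with no allowance for clustering.

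**Step 2: effect of shared counselors on the planned test.** Assumptions, none given in the article: m clients per counselor, equal caseloads; ICC of 0.05 to 0.10 in the counseling arm; no clustering in the wait-list arm; equal total variance in both arms; 64 completers per arm. For the ANCOVA, the ICC is that of the baseline-adjusted residuals. The calculation is for a two-group contrast, not for the full MANOVA.

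The variance of the arm difference, relative to independence, is

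f = [2 + (m − 1) × ICC] / 2.

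The true standard error is √f times the one that the planned test uses. The true two-sided error of a nominal 5% test is

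2 × [1 − Φ(1.96 / √f)].

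Example: with m = 4 and ICC = 0.05, f = (2 + 0.15) / 2 = 1.075 and √f = 1.037. Then 1.96 / 1.037 = 1.89, which gives 5.9%.

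| Clients per counselor (m) | f, ICC 0.05 to 0.10 | √f | True two-sided error |
|---|---|---|---|
| 1 | 1.000 | 1.000 | 5.0% |
| 2 | 1.025 to 1.050 | 1.012 to 1.025 | 5.3 to 5.6% |
| 4 | 1.075 to 1.150 | 1.037 to 1.072 | 5.9 to 6.8% |
| 8 | 1.175 to 1.350 | 1.084 to 1.162 | 7.1 to 9.2% |

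**Step 3: what the caseloads imply.** For 80 counseled participants, m = 2 means 80 / 2 = 40 counselors, m = 4 means 20 and m = 8 means 10.

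**Step 4: power.** Without baseline adjustment, power is Φ(0.5 × √32 / √f − 1.96). This gives 80.7% at m = 1, 78–75% at m = 4 and 74–68% at m = 8. With baseline adjustment, the residual variance is multiplied by 1 − r², where r is the baseline–outcome correlation (assumed). At r = 0.5 the factor is 0.75, and power is about 90% without clustering, 88% at m = 4 with ICC 0.05, and 80% at m = 8 with ICC 0.10. At r = 0.3 the factor is 0.91, and power is about 82% at m = 4 with ICC 0.05. At m = 8 with ICC 0.10 it is Φ(2.828 / (0.954 × 1.162) − 1.96) = Φ(0.59), about 72%.

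**The case against.** The strongest objection is that the article never says counselors share trial clients, and without sharing there is no problem. The one relevant figure points away from heavy sharing: 300 / 80 = 3.75 candidates per counseled participant. Section 2.1.1 also requires voluntary participation throughout and screens on willingness to do grief counseling. A caseload of 8 would need only about 10 counselors, and nothing in the article suggests so few. Caseload and session format are also details that a journal article may leave to the full protocol.

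Much of this stands. Sharing is not established, and silence on caseload is not itself a defect. But a pool larger than the arm only makes one client each possible. Section 2.1 describes the 300 as candidates before screening, and no section commits those trained to deliver Study 3. What the article does fix is a pair of models that are valid only if sharing is absent or negligible.

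A reader might also infer that the stated 80% power is too high. The documents do not support that. The sample-size calculation takes no credit for the baseline adjustment that section 3 plans, and step 4 shows that this adjustment could offset the loss at modest caseloads. Power would fall short only with heavier sharing, very few counselors or a weak baseline correlation, none of which the article indicates.

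**Conclusion.** The point holds conditionally. The planned Study 3 tests ignore the counselor, and if counselors see several trial clients those tests are anti-conservative. The excess is negligible at 2 clients each, up to about 2 percentage points at 4, and about 2 to 4 points at 8. These figures rest on an assumed ICC of 0.05 to 0.10, equal caseloads and individual sessions. Group sessions would add a further layer of clustering. At one client per counselor the planned analysis is sound.

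This is not a demonstrated error, and no conclusion about the stated power follows. It is a cheap safeguard for the validity of the main comparison, of low to moderate severity.

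**What to change.** Record the ID of the counselor who sees each Study 3 participant, and state in advance a rule of this kind:

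- If each counselor takes one trial participant, the planned baseline-adjusted ANCOVA stands. A counselor effect could not then be separated from a difference in residual variance between the arms, so the more complex model would add nothing useful.
- If any counselor sees more than one trial participant, analyze with a partially nested mixed model: baseline score as covariate, a random counselor effect in the counseling arm only, and Satterthwaite degrees of freedom. The mixed-model procedure in SPSS, the package named in section 3, can fit this.

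The cost is one extra recorded variable, a change of analysis wording and slightly wider intervals where counselors are shared: about 1–2% wider at 2 clients each and 4–7% at 4, from √f above, and somewhat more if few counselors leave few degrees of freedom. No additional participants are required for this change. Counselor ID is easiest to collect as sessions take place, so the decision is best made before counseling starts.

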## 4. Discussion

Increasing attention has been paid to bereavement-related disorders in recent decades. Grief is an inevitable experience for each human being. But adjustment to loss has substantial variations between individuals, and various responses to loss follow several distinct trajectories [4,8]. After the initial period of losing a loved one, some people may gradually adapt to their new life and move on with the love and memories of the deceased; for others, however, there are some factors that may hinder their adjusting process to grief; and for a few people, negative mental and physical health consequences may be extreme and persistent after loss [4,32]. Grief resulting from the loss of a loved one due to COVID-19 may be complicated with several factors (e.g., experiencing multiple losses, lack of traditional rituals) and may thus prove to be more persistent or extreme.

The trajectories of bereavement could be affected by socio-cultural factors. According to previous research, bereaved parents in China presented different patterns of grief symptoms (e.g., higher levels of loneliness, emptiness, and numbness) compared to Swiss bereaved parents [44,45]. Therefore, it is necessary to explore grief reactions and assess the effectiveness of grief therapy in different cultural backgrounds. This research will provide valuable insight into grief research and grief counseling in China, as well as providing professional mental health services for individuals who may develop grief-related disorders in the future.

Considering the large number of bereaved individuals who are suffering from grief and other mental health problems, it is significant to develop a suitable and effective intervention protocol immediately. With this research, we hope to help fill in the gap in the research and therapy of bereaved individuals during COVID-19 in China.

To the best of our knowledge, this will be the first time that such a large-scale grief research project will have been conducted among bereaved individuals in mainland China during COVID-19 pandemic. This project will carry positive implications for practice, research, policy.

In terms of practical significance, this project will be beneficial to increasing understanding of the mental health status of the bereaved individuals, and promoting awareness of mental health in China. Since there are very few professional grief counselors in mainland China, one of the aims of this project is to provide grief theory and grief counseling training to experienced counselors, to improve their competence, and provide professional grief counseling services for bereaved individuals in the future. This research develops, conducts, and evaluates the training program of grief counselling in mainland China for the first time, which will largely promote the development of grief counseling in China.

From a research perspective, as far as we know, this is the first study in mainland China to explore the training effect of grief counselors, and to evaluate the efficacy of RCT grief counseling for bereaved individuals. This study is rooted in China’s local culture and policy conditions. This study may improve grief theories under the background of Chinese culture, expands the depth and breadth of grief research culturally, and also provides theoretical support for further grief research and grief intervention.

As for policy perspective, China’s mental health work is still in its infancy. Our project may help raise awareness of the area of grief, and promote the development of policies for the physical and mental health of the bereaved individuals.

## 5. Ethics, Consent and Permissions

This research will follow the latest version of the Declaration of Helsinki. The study protocol was approved by the Institutional Ethics Committee of Beijing Normal University and the Chinese clinical trial registry has approved the study (Register ID: ChiCTR2000038255). Informed consent to participate in the study will be obtained from all participants. Participants will be informed that they can withdraw at any time from the study without consequences.

